### Outcome measures

The questionnaire obtained at T0 provides background information including: sex, age, education level, born in Sweden or not; adolescent/parents born in Sweden or not; living situation (adolescent)/marital status (guardian); number and order of siblings. For guardians, employment is also required. Person-reported outcome measures are linked to empowerment and PCC by evaluating the personal determinants of generic and illness specific nature (knowledge, self-efficacy and self-management skills).^18^

### Primary outcome measures

#### Empowerment

The primary outcome is empowerment. Empowerment is measured with the Gothenburg Young Persons Empowerment Scale (GYPES).^29^ This scale has been tested in a cross-sectional study in order to determine its psychometric properties in adolescents with CHD and T1D and supporting GYPES validity and reliability as a tool for assessing young persons’ empowerment.^26^ The five subscales measure: (1) self-perceived level of understanding of their disease (knowledge and understanding); (2) the capacity patients have to handle their disease (personal control); (3) the effect their illness has on their lives and sense of self (identity); (4) the capacity to make decisions along with the healthcare professional (shared decision-making); and (5) the ability to share their experiences and help others who are going through a similar situation (enabling others). The primary outcome, analysed at T2, is the total score ranging from 15 to 75 points, with a higher score reflecting a higher level of empowerment.^29^

### Secondary outcome measures

The secondary outcome variables chosen are other important developmental tasks in adolescence and emerging adulthood and in relation to T1D. When evaluating interventions aimed at improving the outcome of young adults with T1D, some recommended core outcomes are set.^30^ These eight outcomes are: measures of diabetes-related burden or stress, diabetes-related quality of life (QoL), number of severe hypoglycaemic events, self-management behaviour; number of instances of diabetic ketoacidosis (DKA), objectively measured HbA1C, level of clinic engagement and perceived level of control over diabetes. In addition, we measure indicators for successful transition and transfer outcomes as proposed by Coyne *et al*,^31^ which include clinic attendance, hospitalisation rates, disease-specific outcomes and transfer-specific satisfaction. See table 1 for an overview of included variables and measurements. Secondary outcomes include endpoint at T2 and change from baseline to T2 (also empowerment), while the subscales in questionnaires will be included in exploratory analyses.

**Table 1 T1:** Overview of variables and measurements in Stepstones-DIAB

Variables/indicators	Measurement	Time point	Source

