**Transfer specific**			
Transition readiness	Readiness for Transition Questionnaire^38^	T0, T1, T2	A+P
Uncertainty (parents)	Uncertainty Scale (Linear Analogue Scale)^39^	T0, T1, T2	P
Clinical indicators	Clinic attendance rates, pretransfer and post-transfer Time between last visit in PC and first visit in AC	T2	Admin
Transitional Care Experiences Questionnaire	In progress	T2	A

A, adolescents; AC, adult care; CGM, continuous glucose monitoring; CSII, continuous Ssubcutaneous Iinsulin Iinfusion; HbA1c, glycated haemoglobin; isCGM, intermittent scanning continuous glucose monitoring; MDI, multiple daily injection; NDR, National Diabetes Registry; p, parents; PC, paediatric care; SMBG, self-monitoring blood glucose testing.

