#### Diabetes specific

Diabetes duration, insulin administration (multiple daily injections or continuous subcutaneous insulin infusion), blood glucose testing (self-monitoring blood glucose testing/continuous glucose monitoring, CGM/intermittent scanning CGM) are descriptive variables. Hypoglycaemic events and DKA will be summed up for the whole study period and compared at T2. HbA1c will be analysed using DCA Vantage (Siemens Healthcare Diagnostics AB, Upplands Väsby, Sweden) and the test results collected from the National Diabetes Register. Analyses will be performed at T2 and change from baseline to T2.

‘Check your Health’ measures self-perceived physical and emotional health, social relationships and general QoL on four vertical thermometer scales ranging from 0 to 100, with 0 indicating low self-perceived health. Each scale indicates self-perceived health with diabetes and, on the same scale, self-perceived health imagined without diabetes. The measured difference between self-perceived health with and the imagined without diabetes is defined as the burden of diabetes.^33^

DISABKIDS Chronic Generic Measure-12 measures general QoL and the level of distress caused by a chronic disease. The short-form of the DISABKIDS chronic generic module consists of 12 five-point Likert-scaled items assigned to the three domains: mental, social and physical. Higher scores represent better outcome.^34–36^

DISABKIDS Diabetes Module consists of 13 five-point Likert scaled items and has two scales: an Impact and a Treatment scale. The Impact scale describes emotional reactions of the need to control everyday life and restrictions of one’s diet. The Treatment scale refers to carrying equipment and planning treatment. Higher scores represent better outcome.^34 36 37^

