### Data analysis

The primary endpoint (total score of the level of empowerment at T2) will be analysed using Fisher’s non-parametric permutation test unadjusted between the intervention group and the control group in the RCT on the Full Analysis Set with imputation of missing values using stochastic imputation. A sensitivity analysis will be conducted with analysis of covariance (ANCOVA) adjusting for stratification variables without imputation. If confounders are found, complementary analyses will be conducted using ANCOVA between the two groups adjusted for these confounders. A confounder is a baseline variable that differs between the groups and influences the primary outcome variable. For comparison between the two randomised groups, Fisher’s non-parametric permutation test will be used for continuous variables, Fisher’s exact test for dichotomous variables, Mantel-Haenszel X^2^ test for ordered categorical variables and Pearson X^2^ test for non-ordered categorical variables. Missing data will be handled with stochastic imputation. Mean difference between the two groups with 95% CI will be presented for all continuous and dichotomous variables. For comparison within groups, Fisher’s non-parametric permutation test for paired observation will be used for continuous variables and Sign test for dichotomous variables and ordered categorical variables.

All analyses will be predefined in a detailed statistical analysis plan before data base lock. In a later stage, a comparison between the intervention group and a youth clinic group (study arm 3) will also be performed. All significance tests will be two sided and conducted at the 5% significance level.

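### Scored secondary outcomes with a baseline are each tested in two versions (T2 value and change) at an unadjusted 5%, and nothing says which version counts

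*Protocol article*

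**What the plan says.** All references are to the protocol article.

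- **Secondary outcome measures** defines two versions: "Secondary outcomes include endpoint at T2 and change from baseline to T2 (also empowerment"). It sets only one group apart as exploratory: "the subscales in questionnaires will be included in exploratory analyses".
- **Diabetes specific** repeats the two versions for HbA1c: "Analyses will be performed at T2 and change from baseline to T2". Two event counts are handled differently: "Hypoglycaemic events and DKA will be summed up for the whole study period and compared at T2".
- **Table 1** gives a T2 time point only for the clinical indicators ("Clinic attendance rates, pretransfer and post-transfer Time between last visit in PC and first visit in AC") and for the "Transitional Care Experiences Questionnaire", so these have no change from baseline.
- **Data analysis** states: "All significance tests will be two sided and conducted at the 5% significance level". Continuous variables are compared between the randomised groups with Fisher's permutation test. Covariate adjustment appears only in the sensitivity and complementary analyses, described in connection with the primary outcome. Details are deferred to a statistical analysis plan due before database lock.
- **Primary outcome measures** names a single primary endpoint, the total GYPES score at T2.

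**The concern.** In a randomised comparison the two groups have the same expected baseline. The between-group difference at T2 and the between-group difference in change therefore estimate the same treatment effect, and they differ only through chance imbalance at T0. Testing both without adjustment gives each outcome two chances of a significant result. When the versions disagree, the article offers no rule for which one supports the conclusion.

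The outcomes concerned include HbA1c, quality of life and transition readiness, and the Dissemination section foresees discussing findings with healthcare representatives with a view to implementation. A reader who sees one significant version of an outcome could not tell from the article what error rate stands behind it.

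**Working it through.** **The plan's own figure.** The article gives no error rate for the secondary outcomes. Its sample size for the primary outcome reproduces: n = 2(1.96 + 0.8416)² / 0.5² = 62.8, so 63 per arm, and 63 / 0.90 = 70. The primary outcome has one test at 5% and is not in question.

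**Counting the tests, at the level of whole scales (Table 1).**

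- Two versions each: health behaviour, HbA1c, diabetes burden, DISABKIDS generic, DISABKIDS diabetes module, transition readiness (adolescent), transition readiness (parent), parental uncertainty. That is 8 × 2 = 16.
- One version each: hypoglycaemic events, DKA, clinic attendance, time between last paediatric and first adult visit, experiences questionnaire. That is 5.
- Total: 16 + 5 = 21. Adding change in empowerment gives 22, and counting attendance before and after transfer separately gives 23.

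**One outcome with no effect.** Let ρ be the correlation between T0 and T2, with equal variance σ² at both times. The article does not give ρ, so 0.3 to 0.7 is an assumption.

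- Cov(T2, T2 − T0) = σ²(1 − ρ) and SD(T2 − T0) = σ√(2(1 − ρ)).
- The two test statistics therefore correlate at (1 − ρ)/√(2(1 − ρ)) = √((1 − ρ)/2).
- P(at least one significant) = 5% + 5% − P(both), and P(exactly one) = 10% − 2 × P(both). P(both) comes from the bivariate normal distribution with cut-off ±1.96.

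| ρ | correlation of the two tests | P(both) | P(at least one) | P(exactly one) |
|---|---|---|---|---|
| 0.3 | 0.592 | 1.22% | 8.78% | 7.6% |
| 0.5 | 0.500 | 0.93% | 9.07% | 8.1% |
| 0.7 | 0.387 | 0.65% | 9.35% | 8.7% |

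**The family of 21 tests, no true effect on any.** These are simulated correlated z-statistics. The between-outcome correlation is also an assumption. Each range covers ρ from 0.3 to 0.7.

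| between-outcome correlation | any false positive, either direction | any favouring the programme | 13 single tests, either direction |
|---|---|---|---|
| 0 | 63–65% | 38–40% | 49% |
| 0.3 | 56–58% | 29–31% | 42% |
| 0.5 | 46–49% | 24–25% | 33% |
| 0.8 | 29–31% | 14–16% | 19% |

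With the 23-test count, the either-direction rate is about 49% at between-outcome correlation 0.5 and 1 − 0.95²³ = 69% if all tests were independent. The favourable rate is 25% and 1 − 0.975²³ = 44% respectively.

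**Precision of the alternatives.** Taking the variance of the unadjusted T2 difference as 1, the change difference has variance 2(1 − ρ) and the T2 difference adjusted for T0 has 1 − ρ².

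| ρ | T2 unadjusted | change | T2 adjusted for T0 |
|---|---|---|---|
| 0.3 | 1 | 1.4 | 0.91 |
| 0.5 | 1 | 1.0 | 0.75 |
| 0.7 | 1 | 0.6 | 0.51 |

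The adjusted comparison has the lowest variance in every row.

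**The case against.** The case against rests on four arguments.

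1. **The secondary outcomes are not set up as confirmatory.** Both stated hypotheses concern empowerment, the trial is sized on one primary endpoint, and no section says that a significant secondary result would establish effectiveness. This stands. A reader might infer from the exploratory label on subscales alone that the other secondary outcomes are formal claims, but the article does not say so.

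2. **Test order and multiplicity rules usually sit in the analysis plan, which is not shown.** This stands for a hierarchy, whose absence here is no finding. A fixed sequence would also be compatible with the 5% sentence, since each step is tested at 5%. The objection does not dispose of the two versions, because the article itself makes both of them secondary outcomes and sets their level.

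3. **Stronger summaries fail.** A reader might infer that every secondary outcome is tested twice. Five or six are compared once. A reader might also infer that a false finding in favour of the programme is about as likely as not. The 46% to 49% at between-outcome correlation 0.5 counts results in both directions, and the favourable share is 24% to 25%. At whole-scale level it stays below 50% throughout.

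4. **Most of the family rate comes from having many outcomes, not from duplication.** This is correct: 13 single tests still give 33% at correlation 0.5. The per-outcome doubling does not depend on that count.

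Both versions are publicly declared, CONSORT reporting is promised, and mean differences with 95% CIs are planned. That limits selective reporting but does not say which version leads.

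**Conclusion.** The point holds for the eight scored secondary outcomes that have a baseline. Each has two unadjusted tests of the same effect at two-sided 5%, with no leading version. This raises the per-outcome false positive rate from 5% to about 9% and leaves the two versions in disagreement in about 8% of trials with no effect. These two figures rest only on the assumed baseline-to-T2 correlation (0.3 to 0.7) and vary little across it.

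The family figures (29% to 65% in either direction, 14% to 40% favouring the programme) are much less certain. They depend on an assumed between-outcome correlation of 0 to 0.8, on the count of 21 tests, and on there being no true effect on any secondary outcome. They show how nominal secondary p-values should be read. They do not show that the trial's main conclusion is at risk, because the primary endpoint keeps its 5% error rate.

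**What to change.** 1. In Secondary outcome measures, Diabetes specific and Data analysis, name one test for each scored secondary outcome with a baseline: the between-group difference at T2 adjusted for that outcome's own T0 value. Show raw change from baseline descriptively. The T0 values are already collected, and ANCOVA is already in the plan for the primary sensitivity analysis.
2. State in Data analysis that secondary results are supportive and are reported as estimates with 95% CIs. A short fixed test sequence after the primary is optional. It is needed only if the team wants to make formal secondary claims.

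The first change returns each outcome to a single 5% test, removes the conflict between versions, and gives lower variance than either present version. It does not control the family rate, which is why the second statement is needed. The cost is wording in the protocol and the analysis plan before database lock, with no more patients or data. The downside is that fewer secondary results can be called significant.

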**Primary outcome**			
Patient empowerment	Gothenburg Young Persons Empowerment scale (DIAB)^29^	T0, T1, T2	A
**Secondary outcomes**			
**Generic**			
Health behaviour	Health Behaviour Scale^32^	T0, T1, T2	A
**Diabetes specific**	Diabetes duration Insulin administration (MDI/CSII) Blood glucose testing (SMBG/CGM/isCGM)	T0	NDR
Glycaemic control	HbA1c, hypoglycaemic events, diabetic ketoacidosis	T0, T1, T2	NDR
Diabetes burden	Check your health^33^	T0, T1, T2	A
HRQoL/level of control	DisabKids Chronic Generic Measure-12^34–36^ Disabkids Diabetes Module-10^34 36 37^	T0, T1, T2	A
**Transfer specific**			
Transition readiness	Readiness for Transition Questionnaire^38^	T0, T1, T2	A+P
Uncertainty (parents)	Uncertainty Scale (Linear Analogue Scale)^39^	T0, T1, T2	P
Clinical indicators	Clinic attendance rates, pretransfer and post-transfer Time between last visit in PC and first visit in AC	T2	Admin
Transitional Care Experiences Questionnaire	In progress	T2	A

A, adolescents; AC, adult care; CGM, continuous glucose monitoring; CSII, continuous Ssubcutaneous Iinsulin Iinfusion; HbA1c, glycated haemoglobin; isCGM, intermittent scanning continuous glucose monitoring; MDI, multiple daily injection; NDR, National Diabetes Registry; p, parents; PC, paediatric care; SMBG, self-monitoring blood glucose testing.

#### Generic

Health behaviours are measured with the Health Behaviour Scale. This questionnaire has been validated in adolescents with CHD but is also considered to be valid for the diabetes group. Health behaviours are activities a person undertakes to maintain or improve health and prevent diseases. This scale assesses alcohol consumption, tobacco use, dental care and physical activity. The scale has 15 items that help to calculate three summary risk scores: substance use (score 0–100), dental hygiene (score 0–100) and total health risk score (score 0–100). Higher risk scores represent unhealthier behaviours.^32^

#### Diabetes specific

Diabetes duration, insulin administration (multiple daily injections or continuous subcutaneous insulin infusion), blood glucose testing (self-monitoring blood glucose testing/continuous glucose monitoring, CGM/intermittent scanning CGM) are descriptive variables. Hypoglycaemic events and DKA will be summed up for the whole study period and compared at T2. HbA1c will be analysed using DCA Vantage (Siemens Healthcare Diagnostics AB, Upplands Väsby, Sweden) and the test results collected from the National Diabetes Register. Analyses will be performed at T2 and change from baseline to T2.

‘Check your Health’ measures self-perceived physical and emotional health, social relationships and general QoL on four vertical thermometer scales ranging from 0 to 100, with 0 indicating low self-perceived health. Each scale indicates self-perceived health with diabetes and, on the same scale, self-perceived health imagined without diabetes. The measured difference between self-perceived health with and the imagined without diabetes is defined as the burden of diabetes.^33^

DISABKIDS Chronic Generic Measure-12 measures general QoL and the level of distress caused by a chronic disease. The short-form of the DISABKIDS chronic generic module consists of 12 five-point Likert-scaled items assigned to the three domains: mental, social and physical. Higher scores represent better outcome.^34–36^

DISABKIDS Diabetes Module consists of 13 five-point Likert scaled items and has two scales: an Impact and a Treatment scale. The Impact scale describes emotional reactions of the need to control everyday life and restrictions of one’s diet. The Treatment scale refers to carrying equipment and planning treatment. Higher scores represent better outcome.^34 36 37^

#### Transfer specific

The Readiness for Transition Questionnaire (adolescent and parent version) examines two aspects. First, the overall transition readiness is assessed, using two items ranging from 1 to 4. The sum of these two items results in a score ranging from 2 to 8. Second, the frequency of adolescent responsibility and parental involvement are reported for 10 different health behaviours on a four-point Likert scale. Each variable results in a total score ranging from 10 to 40, with higher scores indicating higher adolescent responsibility or parental involvement, respectively.^38^

Parental uncertainty is measured using a 10 cm Linear Analogue Scale (LAS) with the end points ‘not uncertain at all’ (=0) and ‘extremely uncertain’ (=100). Parental uncertainty comprehends parents’ perceptions of certainty/uncertainty prior to their child’s transfer to adult care. This LAS was developed for an ongoing study in the STEPSTONES-CHD project and has been used in a cross-sectional study.^39^

The new questionnaire on transfer and transition experiences is under construction and will be tested on young persons aged 19–21 years with long-term conditions and experience of the transfer to adult care in order to evaluate its psychometric properties.

Clinical indicators, such as attendance for scheduled outpatient visits before and after transfer to adult clinic and the duration between last visit in paediatric care and the first in adult care, will be collected from the medical record.

Information about validity, reliability and responsiveness of the questionnaires is provided in a online supplementary file.^29 32–35 37–40^

10.1136/bmjopen-2019-036496.supp1Supplementary data

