### Intervention

#### Transition programme (intervention group)

A multicomponent intervention, adapted from the brief transition programme of Hilderson *et al*^23^ and the STEPSTONES-CHD project,^16^ will be implemented. This transition programme comprises eight key components: (1) a TC; (2) a person-centred written transfer plan; (3) provision of information and education about T1D and treatment, health behaviours, dealing with school, friends, leisure activities and the importance of treatment adherence; (4) high access to the TC via telephone/sms; (5) information about and contact with the adult diabetes care team; (6) meeting with other young people with T1D; (7) support for and guidance of parents and (8) the actual transfer to the adult diabetes outpatient clinic. The components are implemented in five steps: (1) first visit with TC at the diabetes paediatric outpatient clinic at the age of 16 years; (2) second visit with TC at the diabetes paediatric outpatient clinic at the age of 17 years; (3) ‘adolescent day’ group information with parents and adolescents, with the participation of healthcare professionals from the adult outpatient clinic and young adults with T1D; (4) third visit with TC at the diabetes outpatient clinic at the age of 18 years and (5) the current transfer to one of the eight adult outpatient clinics that care for adults with T1D in the area (figure 1). The intervention is delivered by specialised trained paediatric nurses at the two paediatric diabetes outpatient clinics (study arm 1 and 2). The content of the patient education is adapted to T1D.

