### Data collection

Baseline data will be collected when participants (the adolescent and one or two parents) have agreed to participate in the study. Participants are asked to complete the set of pen-and-paper questionnaires at 16, 17 and 18.5 years of age (figure 1). These are sent by post to the participants’ home address before the next scheduled outpatient visit. The pack contains an instruction letter, a set of questionnaires and a prepaid and addressed reply envelope. Baseline data (T0) will be collected before any intervention is started (study arm 1). For T0, the most recent HbA1c value before inclusion in the study will be used. It is estimated that the questionnaires will take approximately 30 min to complete. Participants will be asked to complete the set of questionnaires themselves and to return them within 3 weeks. If the questionnaires are not returned within this time frame, patients will be reminded by a new set of questionnaires or asked to complete them while waiting in the waiting room at the next visit.^16 28^

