A challenge in complex interventions like transition programmes is the multiple interacting components and behaviours required by those delivering and receiving the intervention. To evaluate the full extent of a complex intervention in addition to effectiveness, the evaluation must incorporate process assessments of how the intervention is being delivered in practice and what causal mechanisms lead to the desired outcomes. Based on the experiences from the more extensive process evaluation undertaken in STEPSTONES-CHD,^17^ we have identified certain process evaluation components that also need to be undertaken in STEPSTONES-DIAB in order to promote future implementation. These components reflect what is delivered (fidelity, adherence, dose, reach, acceptability) and are provided through participant observations, the intervention implementation form, enrolment form and transition plans.^17^

Some limitations need to be acknowledged in this study. First, this intervention focuses on preparation for transition to adulthood and the actual transfer to adult care. Additional interventions may be needed to secure continuity of care after transfer. Second, the lack of blinding procedures poses a limitation in that the nature of study makes blinding patients and TCs impossible. Third, the short follow-up period of 6 months at the age of 18.5 years cannot be considered enough to evaluate long-term effects of the transition programme. There is a great need to evaluate such effects^9^ and these must be followed up in separate studies after additional consent and funding.

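### The general analysis rules have no provision for right-censoring, so the time from last paediatric to first adult visit would be analysed as an ordinary continuous variable with imputation

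*Protocol article*

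**What the plan says.** Table 1 of the protocol article lists "Time between last visit in PC and first visit in AC" among the transfer-specific secondary outcomes, at T2 only and from an administrative source. The Transfer specific section adds that "the duration between last visit in paediatric care and the first in adult care, will be collected from the medical record". In the same table row and the same sentence, attendance at scheduled visits before and after transfer is a separate indicator.

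Three places fix the timing. The Data collection section says "Participants are asked to complete the set of pen-and-paper questionnaires at 16, 17 and 18.5 years of age", so T2 is at 18.5 years. The Intervention section gives the last programme step before transfer as the "third visit with TC at the diabetes outpatient clinic at the age of 18 years". The Discussion refers to "the short follow-up period of 6 months at the age of 18.5 years".

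The Data analysis section then sets rules by type of variable for the randomised comparison: "Fisher’s non-parametric permutation test will be used for continuous variables", with a mean difference and 95% CI, and "Missing data will be handled with stochastic imputation". It lists tests for dichotomous, ordered and unordered categorical variables. It lists none for time to event and makes no exception for any variable. It also promises a detailed SAP before database lock, which is not at hand.

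**The concern.** A duration that ends with the first adult visit is complete only for adolescents who have made that visit. With record collection about 6 months after transfer, some may not have done so. For them the duration is not unknown in the ordinary sense: it is known to exceed the time observed. That is right-censoring. A missing-data rule discards this information.

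If the imputed values come from observed durations, a late or absent arrival receives the time of someone who arrived. Dropping these adolescents makes the same selection. Both condition on arrival, which happens after randomisation and which the programme may influence, since contact with the adult team and the transfer itself are among its components. If one arm has more adolescents not yet seen, the comparison omits what sets that arm apart, and the estimated difference tends to shrink. The Introduction names poor clinic attendance after transfer as a risk factor, so the affected adolescents are those on whom the indicator should be informative.

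**Working it through.** **The article's own figures.** There is none for this variable. The only design figure concerns the primary outcome: n = 2 × (1.960 + 0.842)² / 0.5² = 62.8, so 63 per arm, and 63 / 0.9 = 70. Both match the Proposed sample size section and do not depend on this point.

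**Follow-up window.** Third coordinator visit at 18 years, T2 at 18.5 years: 18.5 − 18 = 0.5 years, or about 6 months, as the Discussion says. The clock for this variable starts at the last paediatric visit, whose date varies, so individual windows will vary around this.

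**Illustration 1: attenders only, against the restricted mean.** Assumptions, none from the article: exponential times, a 6-month window, and a share p seen by 6 months.

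- Rate: λ = −ln(1 − p) / 6
- Mean among those seen: 1/λ − 6(1 − p)/p
- Restricted mean over 6 months: p/λ

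For p = 0.90: λ = 0.3838 and 1/λ = 2.606. The mean among those seen is 2.606 − 0.667 = 1.94 months; the restricted mean is 0.90 × 2.606 = 2.35.

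For p = 0.75: λ = 0.2310 and 1/λ = 4.328. The mean among those seen is 4.328 − 2.000 = 2.33 months; the restricted mean is 0.75 × 4.328 = 3.25.

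| Seen by 6 months (two arms) | Difference, attenders only | Difference, restricted mean | Ratio |
|---|---|---|---|
| 90% vs 75% | 0.39 months | 0.90 months | 43% |
| 90% vs 80% | 0.29 months | 0.64 months | 45% |
| 95% vs 80% | 0.54 months | 1.08 months | 50% |

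This is a complete-case calculation. Random draws from the same arm's observed times would give the same expected difference. Other imputation models need not.

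**Illustration 2: simulated imputation.** Assumptions: exponential times with the means below, a 6-month window, 70 per arm, 1,000 simulations. Adolescents not seen receive a single random draw from observed times, either within arm or pooled over arms. A t-test stands in for the permutation test. The comparator is a log-rank test censored at 6 months.

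| Mean time (months) | Not seen by 6 months | Power, within-arm draws | Power, pooled draws | Power, censored log-rank |
|---|---|---|---|---|
| 3 vs 4 | 13.5% vs 22.3% | 18% | 10% | 35% |
| 3 vs 6 | 13.5% vs 36.8% | 38% | 21% | 94% |
| 4 vs 8 | 22.3% vs 47.2% | 30% | 11% | 91% |
| 6 vs 12 | 36.8% vs 60.7% | 28% | 7% | 85% |

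With no true difference (3 vs 3), the rejection rates were 7.9%, 4.7% and 5.6% in the same order. Several of these scenarios assume heavy non-arrival. They show the direction and mechanism and do not predict this trial.

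**The case against.** The strongest reply is that the article nowhere says what it would do with this variable. It names no test for it, does not say that the absence of an adult visit is coded as missing, and does not describe the imputation model. Variable-level detail is normally left to the SAP, which is promised and could treat non-arrival as censored. This stands in part. A reader might infer that non-arrivers are in fact given the times of those who arrived, but the documents do not say so; it is only what follows if the general rules are applied as written. The point survives because the article is not silent: it fixes a test, an effect measure and a missing-data rule that cover any continuous variable and do not suit this one.

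A second reply is that non-arrival is not lost, because attendance at scheduled visits after transfer is its own secondary outcome. This also stands in part. A reader might infer that failed transfers vanish from the trial's evidence; they should show, at least partly, in that outcome. Attendance at scheduled visits does not, however, measure delay.

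A third reply concerns size. The attendance shares are assumed, times under scheduled care need not be exponential, and the 43% to 50% ratio compares attenders only with a restricted mean. A reader might infer that the planned analysis recovers about half of the contrast; the ratio does not model the planned imputation, whose form is not given. Nor is a reversed sign supported: every scenario shows attenuation in the right direction. If nearly everyone is seen within 6 months, the effect is small.

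**Conclusion.** The point holds conditionally. Under the rules in the Data analysis section, a right-censored secondary indicator would be analysed as an ordinary continuous variable, and adolescents not yet seen in adult care would fall under the imputation rule. Imputing from observed durations, or dropping these adolescents, tends to attenuate any difference between arms. The size for this trial cannot be computed, because the article gives no non-arrival rate. Under exponential times with 75% to 95% seen by 6 months, the difference among attenders is roughly half the restricted mean difference; with heavier non-arrival, simple imputation loses much of the power of a censored analysis. The primary analysis of empowerment and the sample size are untouched. The plan should change this, but it does not threaten the trial's main conclusion.

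**What to change.** State in the SAP that an adolescent with no adult visit by T2 is censored at the T2 record review and that this variable is exempt from imputation. Analyse time from last paediatric visit to first adult visit with Kaplan-Meier curves by arm, a log-rank test stratified by the randomisation factors (centre, sex and HbA1c group, with sparse strata pooled), and/or the difference in restricted mean time over the follow-up available. Report the proportion in each arm with an adult visit by T2 alongside the planned attendance rates.

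The cost is a few lines of SAP text and one standard additional secondary analysis. The data source is unchanged, provided that the date of the T2 record review is recorded for each adolescent.
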